#### Diagnosis of Cardiac Arrest of Cardiac Origin

In order to verify the diagnostic accuracy of Dispatch Officers, the status of a cardiac arrest victim will be confirmed using the Utstein definition for cardiac arrest of cardiac origin [1].

Cardiac arrest will first be documented at the scene by the paramedic crew, and subsequently confirmed by the base hospital physician or coroner. Cardiac arrest will be defined as per the Utstein criteria for reporting data on cardiac arrest research.

#### Agonal breathing

Can be defined as abnormal breathing, gurgling sound, moaning, or otherwise. Dispatchers Officers are required by protocol to inquire about the presence or absence of agonal or abnormal breathing. A research assistant at each base hospital will systematically review the recordings of all cardiac arrest calls, and use a piloted data collection form to independently document the presence or absence of agonal breathing, as described by the 9-1-1 caller to the Dispatch Officer. Consistency in recognizing agonal breathing among research assistants will be assured with the use of training 9-1-1 communication material before the study starts.

#### Successful Completion of Dispatch-Assisted CPR Instructions

is defined as CPR instructions provided by a Dispatch Officer to a 9-1-1 caller reporting a cardiac arrest victim, resulting in the administration of chest compressions to that victim by a bystander before EMS arrival. Once again, a research assistant will systematically review the recordings of all cardiac arrest calls using a standardized and piloted data collection form in order to collect information on variables pertaining to the successful delivery of dispatch-assisted CPR instructions. Paramedics are required by protocol to document if bystander CPR was ongoing before their arrival.

#### Bystander CPR

"Bystander" CPR is performed by a person who is not part of an organized emergency medical system. The presence or absence of ongoing bystander CPR will be assessed by the first member of the emergency response team to arrive at scene, and will be documented.

#### Survival to Hospital Discharge

is defined as survival of a cardiac arrest victim to hospital discharge. Survival to hospital discharge will be assessed via hospital medical records or via the coroner's office.

### Data analysis

#### Cardiac Arrest Recognition

Sensitivity, specificity and receiver operating characteristic (ROC) curves will be computed.

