## Objectives

The overall goal of this study is to better understand the factors leading to successful dispatch-assisted CPR instructions. This is essential in order to intervene to improve the effectiveness of these instructions, to further improve bystander CPR rates, and to save more victims of cardiac arrest. Specific objectives are to:

1) Determine the ability of Dispatch Officers to correctly diagnose cardiac arrest over the telephone;

2) Quantify the frequency and impact of perceived agonal breathing on cardiac arrest diagnosis by Dispatch Officers;

3) Measure the frequency with which dispatch-assisted CPR instructions can be successfully completed in out-of-hospital cardiac arrest cases; and

4) Measure the impact of dispatch-assisted CPR instructions on bystander CPR rates and survival for out-of-hospital cardiac arrest.

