## Methods

### Study design and setting

This study will combine a before-after design with a prospective cohort design (Figure 1). Objective 4 (bystander CPR and survival rates) will be addressed using a before-after design, the "before" phase occurring prior to 2004, and the prospective "after" phase starting in 2007 (after the run-in period). Objectives 1, 2, and 3 will be addressed with a prospective cohort starting in 2007. The prospective cohort group and the "after" group will be the same group.

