### Study population

All patients with out-of-hospital cardiac arrest (absence of a detectable pulse, unresponsiveness and apnea) meeting the following criteria will be enrolled in the study:

a) presumed cardiac origin;

b) occurring in an eligible study community; and

c) for which resuscitation is attempted by a bystander and/or the emergency responders; or for which dispatch-assisted CPR instructions are being provided.

Case definitions will follow the Utstein Style guidelines for reporting cardiac arrest data [1].

Patients meeting any of the following criteria will be excluded:

a) patients younger than 16 years (cardiac arrest usually respiratory and rare in this population);

b) patients who are "obviously dead" as defined by the Ambulance Act of Ontario (decomposition, rigor mortis, decapitation, or other);

c) trauma victims, including hanging and burns; or

d) patients with cardiac arrests clearly of other non-cardiac origin including drug overdose, carbon monoxide poisoning, drowning, exsanguination, electrocution, asphyxia, hypoxia related to respiratory disease, cerebrovascular accident, and documented terminal illness.

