### Method of assessment and data collection

#### Diagnosis of Cardiac Arrest by Dispatch Officers

According to protocols, Dispatch Officers assume the presence of cardiac arrest when the 9-1-1 caller describes a victim that is lifeless (victim is unresponsive, not breathing, or not breathing normally). Dispatch Officers will notify the medical dispatch centre after every occasion where assisted CPR instructions were initiated. Using a unique identifier, these interventions/cases will later be cross-referenced with the regional cardiac arrest registry for measuring diagnostic accuracy. In addition, a research assistant will later listen to the recordings of each cardiac arrest intervention and document on a standardized and piloted data collection form the reasons why cardiac arrest may not have been recognized by the Dispatch Officer.

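### Specificity and ROC curves are planned for dispatcher recognition of cardiac arrest, but the described data sources contain no true negatives and only a yes/no decision

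*Protocol article*

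**What the plan says.** The first objective in the protocol article is to "Determine the ability of Dispatch Officers to correctly diagnose cardiac arrest over the telephone". On design, the section on study design and setting says "Objectives 1, 2, and 3 will be addressed with a prospective cohort starting in 2007", and that cohort is the same group as the after group.

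The relevant data sources are:

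- **Enrolment:** the section headed Study population has this as its opening rule: "All patients with out-of-hospital cardiac arrest (absence of a detectable pulse, unresponsiveness and apnea) meeting the following criteria will be enrolled in the study". The last inclusion criterion adds cases "or for which dispatch-assisted CPR instructions are being provided", but as a criterion applied to patients in arrest.
- **Dispatcher positives (Diagnosis of Cardiac Arrest by Dispatch Officers):** "Dispatch Officers will notify the medical dispatch centre after every occasion where assisted CPR instructions were initiated".
- **Link to the reference standard (same section):** "these interventions/cases will later be cross-referenced with the regional cardiac arrest registry for measuring diagnostic accuracy".
- **Call review (Agonal breathing, and similarly the section on completion of instructions):** research assistants "will systematically review the recordings of all cardiac arrest calls".

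The whole analysis statement for this objective, under Cardiac Arrest Recognition, is "Sensitivity, specificity and receiver operating characteristic (ROC) curves will be computed".

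**The concern.** Specificity is the proportion of non-arrest calls that the dispatcher correctly leaves without an arrest diagnosis. It needs a count of non-arrest calls, including those in which no instructions were started. The article states how diagnostic accuracy will be measured, and that method has no step that collects or samples such calls. An ROC curve needs specificity too, and also a graded result or a threshold that can be moved. The article describes a decision rule that the dispatcher either applies or does not.

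Two of the three measures named for objective 1 therefore do not fit the article's own data. If they are reported anyway, the figures will reflect a denominator chosen afterwards and not how well dispatchers discriminate.

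**Working it through.** **Plan's own figure.** The article gives no figure for specificity or ROC. Its one computed design figure is the sample size for survival, and it reproduces. With 5% versus 7%, 90% power, two-sided alpha 0.05 (assumed, as alpha is not stated) and pooled variance without continuity correction:

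n = [1.960·√(2·0.06·0.94) + 1.282·√(0.05·0.95 + 0.07·0.93)]² / 0.02² = 2,962 per group after rounding up.

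That figure is not in dispute and is used below only as a cohort size.

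**Which cells the sources fill.**

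| | Arrest | No arrest |
|---|---|---|
| Dispatcher positive | True positive (TP): instruction start matched to registry | False positive (FP): instruction start with no registry arrest |
| Dispatcher negative | False negative (FN): registry arrest without a start | True negative (TN): no source described |

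In the enrolled cohort taken strictly, which is limited to arrests, the whole right-hand column is empty and specificity is undefined. With the dispatch notifications added, FP is filled but TN is not.

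- Sensitivity = TP/(TP + FN): estimable.
- PPV = TP/(TP + FP): estimable, with all instruction starts as denominator.
- Specificity = TN/(TN + FP): not estimable.

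**Illustration of the dependence on TN.** Inputs: 2,962 arrests (Sample size); 56.0% recognised (Ottawa pilot); 14% of instruction starts in error (the Seattle review cited under agonal breathing). Assumptions: the 14% is 1 − PPV, and every recognised arrest leads to an instruction start.

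- TP = 0.56 × 2,962 ≈ 1,659; FN ≈ 1,303
- FP = 1,659 × 0.14/0.86 ≈ 270

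| Assumed TN | Specificity = TN/(TN + 270) | One-point area = (0.56 + specificity)/2 |
|---|---|---|
| 500 | 64.9% | 0.605 |
| 1,000 | 78.7% | 0.674 |
| 5,000 | 94.9% | 0.754 |
| 10,000 | 97.4% | 0.767 |
| 100,000 | 99.7% | 0.779 |

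Dispatcher behaviour is identical in every row; only the assumed denominator changes.

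**Recognition is not initiation.** The 56.0% describes recognition, while the 14% and the dispatch notifications concern starting instructions. In the pilot, instructions were offered to 75.9%; the denominator is not clear. If it is the recognised cases (assumption), TP by initiation is 0.759 × 1,659 ≈ 1,259, FP is 1,259 × 0.14/0.86 ≈ 205, and sensitivity by initiation is 0.56 × 0.759 = 42.5%. Specificity is then 1,000/1,205 = 83.0% with 1,000 assumed true negatives and 100,000/100,205 = 99.8% with 100,000. The dependence on TN remains, and the choice of index test alone moves sensitivity from 56% to 42.5%.

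**ROC.** A yes/no decision gives one interior point (1 − specificity, sensitivity). Joining it to the corners gives an area of (sensitivity + specificity)/2, which adds nothing to the two components and requires the missing one.

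**What the collected data can support.** Under the first set of assumptions, the normal-approximation 95% half-width is 1.96·√(0.56·0.44/2,962) ≈ 1.8 percentage points for sensitivity. For a PPV of 86% among 1,659 + 270 = 1,929 starts it is 1.96·√(0.86·0.14/1,929) ≈ 1.5 points.

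**The case against.** The strongest reply is that the absence of non-arrest calls is inferred from silence in a condensed article, and that the full protocol may define a comparison sample. This has some force: nothing says that only arrest calls are reviewed, and the description of which recordings are heard could include false starts. But false starts add false positives, not true negatives. The article also goes beyond silence, because it fixes the population, the linkage used to measure accuracy, and the measures, and these do not fit together.

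A second reply is that a total call count from the dispatch centres would supply TN by subtraction (calls − TP − FN − FP). That is correct, so specificity is not impossible in principle. However, the article does not say that call totals are collected. Over all medical calls the result would be close to 100% whatever the dispatchers did, and false starts per call would be almost the same quantity as 1 − specificity.

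A third reply is that the reference standard is arrest of cardiac origin, so arrests of other origin could serve as negatives. The exclusion criteria remove them, and they are still arrests, so they say nothing about specificity for recognising arrest.

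Three stronger readings are tempting and are not supported:

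- **Specificity is 0%.** This places false starts on people not in arrest inside a cohort defined as patients in arrest. In that cohort specificity is undefined.
- **False starts would go unreported.** Every start is to be matched to the registry for diagnostic accuracy, and not naming PPV in one sentence is no plan to withhold it.
- **The study's main result is at risk.** The Sample size section makes survival to discharge the main objective, and this sentence does not bear on it.

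**Conclusion.** The point holds. As described, specificity for dispatcher recognition cannot be estimated, and the ROC curve reduces to one point that depends on it. In the illustration specificity runs from 64.9% to 99.7% as the assumed TN goes from 500 to 100,000. That range rests on the 14% being 1 − PPV, on equating recognition with initiation, and on TN values that are wholly assumed. The finding that specificity is not estimable needs none of these; it follows from the sources listed.

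This should be fixed, but it is not critical to the study. It affects objective 1 only. Sensitivity, which captures missed arrests, is estimable, and the survival and bystander CPR comparisons and the sample size are untouched.

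**What to change.** Replace the sentence under Cardiac Arrest Recognition with wording to this effect:

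- Sensitivity among registry-confirmed arrests, with 95% CI.
- Positive predictive value among all instruction starts, and its complement (the proportion of starts on victims not in arrest), with 95% CI. The denominator is the dispatch notifications, not the enrolled arrest cohort.
- For each measure, whether the index test is recognition of arrest or initiation of instructions.

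Drop the ROC curves. Drop specificity unless a non-arrest call population is named and its counts are obtained. Any projected count of false starts should state that the 14% is assumed to be 1 − PPV.

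The replacement measures need a change of wording only and use data the article already says are collected. Keeping specificity would cost more, because the calls or call totals that form its denominator would have to be defined and gathered.

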#### Agonal Breathing

Descriptive statistics with 95% confidence intervals (95%CI), and kappa statistics with 95% CI will be calculated to measure the level of agreement between the dispatcher and the research assistant during the study, and among research assistants using training materials before the study.

#### Dispatch-Assisted CPR Instructions

Descriptive statistics with 95% CIs will be calculated to describe successes in various stages of the implementation of CPR instructions, to describe the caller's receptiveness of the instructions, and various time delays occurring during dispatch-assisted CPR instructions.

#### Bystander CPR and Survival Rates

Descriptive statistics with 95% CIs will be calculated for bystander CPR and survival rates. In addition, two statistical modelling approaches will be considered: 1) A univariate and a stepwise logistic regression analysis to control for potential confounding effects of variables possibly associated with bystander CPR and survival rates. These variables include age, gender, initial cardiac rhythm, and EMS response time intervals. Bystander CPR rates and cardiac arrest survival rates in the "before" phase (prior to 2004) will be compared to the "after" phase (after the run-in period finishing in 2006) controlling for these confounding variables. 2) A time series analysis to analyse trends (quarterly) over the whole study period (including the run-in phase), and identify a possible point of inflection due to the implementation of dispatch-assisted CPR instructions. This will determine if bystander CPR and survival rate inflections are significant, controlling for trends over time. This analysis will be performed for each community and then the results may be combined in a meta-analysis after assessing homogeneity of the results across the communities.

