### Pilot evaluation of dispatch-assisted CPR instructions in Ottawa, Canada

We recently conducted a pilot observational cohort study evaluating the frequency of agonal breathing during cardiac arrest, its impact on the ability of Dispatch Officers to recognize cardiac arrest, and the impact of dispatch-assisted CPR instructions on bystander CPR rates in Ottawa, Canada [85].

Audio recordings of all out-of-hospital cardiac arrest cases over two successive nine-month periods were obtained. The nine-month periods corresponded to the periods before and after the introduction of dispatch-assisted CPR instructions. There were 529 cardiac arrest cases during the two periods between July 1^st^, 2003 and December 31^st^, 2004 [85]. Victim characteristics were similar in the before (N = 295) and after (N = 234) phase: mean age was 68.3, 66.7% were male, collapse was witnessed 50.1% of the time, the mean time interval between 9-1-1 call to vehicle stop at the scene was 6:37 min:sec, VF/VT was present in 29.9%, and survival to hospital discharge was 4.0%. We located 82.1% of 9-1-1 recordings for the after period. Callers were female 63.5% of the time, the victim's spouses 29.2% of the time, and previously trained in CPR 24.0% of the time. Dispatch Officers recognized 56.0% (95% CI 48.9–63.0%) of cardiac arrest cases; agonal breathing was present in 37.0% (95% CI 30.1–43.9%) of all cardiac arrest cases and accounted for 50.0% (95% CI 39.1–60.9%) of missed diagnoses. CPR instructions were offered to 75.9% and accepted by 53.7% of callers; 26.3% declined instructions because of prior CPR training. 17.2% and 8.3% of callers provided ventilations and chest compressions as a result of the intervention. The longest delays occurred between call-to-cardiac arrest diagnosis (2:38), and during ventilation instructions (2:05). Bystander CPR rates increased from 16.7% to 26.4% (AR 9.7%; 95% CI 8.5–11.3% p = 0.006).

Before the introduction of dispatch-assisted CPR instructions, no other intervention had succeeded in improving bystander CPR rates in the community of Ottawa, Canada. The pilot project allowed the authors to determine the feasibility of collecting information of interest. The next logical step is to conduct a large, multi-centre trial in order to best evaluate the impact of dispatch-assisted CPR instructions.

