**Figure 1 F1:**
[figure not shown]
Study design and proposed statistical analyses.

The study will take place in 19 large and small cities located in Ontario, Canada affiliated with 11 base hospital programs. The combined population in those 19 communities is 2,903,887 and ranges between 15,605 and 774,072 (2001 Statistics Canada census). Approximately 1,703 patients suffer cardiac arrest each year and receive treatment in these communities. All communities have sophisticated EMS services with first responding fire fighters and second-tier primary care (BLS-D) and advanced care (ALS) paramedics. All centres have been collecting high-quality data on system and cardiac arrest victim characteristics since 1994, and all have initiated dispatch-assisted CPR instructions between 2004 and 2005.

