### Sample size

The main objective of this study is to measure the effect of dispatch-assisted CPR instructions on survival to hospital discharge for out-of-hospital cardiac arrest victims. The required sample size has been estimated based on a dichotomous response variable from two independent samples (before and after the introduction of dispatch-assisted CPR instructions). The required sample size is based on an expected survival rate of 5% in the before group (based on previous studies conducted in the study communities [8]), an expected survival rate of 7% in the after group (based on mathematical modelling and scientific reports), an average survival rate of 6% for all study participants and a 2% minimal clinically important difference in survival rate. Using these figures and setting power at 90%, 2,962 cardiac arrest victims will be required for each group.

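### The before-after comparison is to be adjusted by stepwise logistic regression, which can drop the confounders it is meant to control; a pre-specified model is affordable and should replace it

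*Protocol article*

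**What the plan says.** The article's Data analysis section, under Bystander CPR and Survival Rates, puts forward two modelling approaches. The first is "A univariate and a stepwise logistic regression analysis to control for potential confounding effects" of variables that may be associated with the two outcomes. On the candidates it says: "These variables include age, gender, initial cardiac rhythm, and EMS response time intervals". It then states that rates before 2004 and after the run-in will be compared with these confounders controlled. It gives no entry or removal rule and no list of forced terms. Neither community nor witnessed collapse is named for this model.

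The second approach is a quarterly time-series analysis run separately in each community, with optional pooling by meta-analysis once homogeneity has been assessed.

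The setting is described thus: "The study will take place in 19 large and small cities located in Ontario, Canada affiliated with 11 base hospital programs". Populations range from 15,605 to 774,072 out of 2,903,887. The Ottawa pilot recorded witnessed status: "collapse was witnessed 50.1% of the time".

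**The concern.** The comparison is not randomised, and the Sample size section calls the effect on survival the main objective. The first model therefore has one job: to estimate a single contrast, after versus before, with confounding removed. Stepwise selection serves a different purpose. It keeps covariates by their p-values for the outcome, so a variable that is weakly prognostic but differs between phases can be discarded, and its confounding then returns to the phase estimate. The reported interval is calculated as if the final model had been chosen in advance. The stated method and the stated promise of control do not fit together.

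A second issue belongs to the same model. It pools patients from 19 communities of very different size. If survival in a community drifts between periods for local reasons, patients in the same community and period are correlated, and a standard error that treats them as independent is too small.

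**Working it through.** **1. Reproduce the plan's sample size.** Inputs from the Sample size section: "expected survival rate of 5% in the before group", "an expected survival rate of 7% in the after group", and "setting power at 90%, 2,962 cardiac arrest victims will be required for each group". Alpha is not stated; two-sided 0.05 is assumed.

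n = [1.960 × √(2 × 0.06 × 0.94) + 1.282 × √(0.05 × 0.95 + 0.07 × 0.93)]² / 0.02² = 2,961.02, rounded up to 2,962. The figure reproduces exactly. The target log odds ratio is ln[(0.07/0.93)/(0.05/0.95)] = 0.358.

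**2. Is selection needed?** Expected survivors: 2,962 × 0.05 + 2,962 × 0.07 = 148 + 207 = about 355.

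| Model for survival | Parameters | Events per parameter |
|---|---|---|
| Phase + 4 named covariates | 5 | 71 |
| + witnessed status | 6 | 59 |
| + 18 community indicators | 24 | 14.8 |

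This counts one parameter per covariate. Four further parameters for rhythm categories or non-linear terms give 355/28 = 12.7. For bystander CPR at the pilot rates (16.7% and 26.4%), expected events are 2,962 × 0.431 = 1,277, or 53 per parameter even with 24 parameters.

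The average hides sparse communities. The smallest holds 15,605/2,903,887 = 0.54% of the population, so about 355 × 0.0054 = 2 survivors over both phases. A random intercept or stratification suits this better than 18 free indicators.

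**3. How much does stepwise selection cost?** The documents give no covariate effects or imbalances, so these are assumptions. Simulation: 2,962 per phase, survival near 5.5%, no true phase effect, phase forced in, one normally distributed confounder removed if p > 0.05, 2,000 runs per setting (Monte Carlo error about 0.5 points).

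| Phase imbalance | Log OR per SD | Dropped | Coverage, fixed | Coverage, stepwise | Stepwise bias (log OR) |
|---|---|---|---|---|---|
| 0.25 SD | -0.10 | 57% | 0.955 | 0.953 | -0.009 |
| 0.25 SD | -0.15 | 26% | 0.945 | 0.944 | -0.003 |
| 0.5 SD | -0.10 | 59% | 0.951 | 0.939 | -0.018 |
| 0.5 SD | -0.15 | 27% | 0.954 | 0.939 | -0.012 |
| 1 SD | -0.10 | 60% | 0.960 | 0.920 | -0.037 |
| 1 SD | -0.15 | 27% | 0.960 | 0.906 | -0.022 |

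The confounder is often dropped, but this matters only when the imbalance is large. The largest bias is about a tenth of the target (0.037/0.358).

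**4. How much does ignoring community-by-period variation cost?** Variance treating patients as independent: 2 × 0.0564/2,962 = 3.81 × 10⁻⁵, where 0.0564 = 0.06 × 0.94. If true community-period rates vary with standard deviation s, add 2s²/K, where K is the effective number of communities. Type I error = 2 × P(Z > 1.96 × SE_naive/SE_true). K = 19 treats the communities as equal in size. K = 10 allows for one of them holding 774,072/2,903,887 = 27% of the population; even with 17 others equal in size, the effective number is then about 9.8.

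| s (assumed) | K = 19 | K = 10 |
|---|---|---|
| 0.5 point | 5.8% | 6.5% |
| 1 point | 8.3% | 11.2% |

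A simulation on another scale, with the phase effect varying between communities by a log-OR SD of 0.1, 0.2 or 0.3, gave about 5%, 7% and 14% (500 runs each, Monte Carlo error about 1 point or slightly more). The order of magnitude agrees.

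**The case against.** The strongest defence is that this is a condensed article. The list of variables is introduced by a word that leaves it open, so witnessed status and community are unnamed, not excluded, and a fuller document may add them. This stands. A reader might infer that the plan omits them, but the text does not support that.

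A reader might also infer that phase could itself be selected out. That would be serious, because under no true effect phase would be retained in only about 5% of analyses and every retained interval would miss the truth. But the text makes phase the contrast and the other variables the adjusters, so this reading is not supported either.

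Nor is community ignored: the time-series approach is run by community. That does not settle how the pooled logistic model handles it.

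Finally, the pilot reports similar victim characteristics in its two phases, which makes a 1 SD imbalance look unlikely. This is fair, although it rests on one city and adjacent nine-month periods, whereas the main study compares years before 2004 with 2007 onwards. Omitting witnessed status would also do little: a 5-point shift between phases biases the log odds ratio by about 0.02 under assumed effects.

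None of this defends the selection step, which is a method the article states.

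**Conclusion.** The point holds in a limited form. The article fixes stepwise selection for a comparison that it also says will control the named confounders, and with about 355 expected survivors there is no statistical reason to select.

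It would go too far to call the adjusted estimate unreliable in general. With phase forced in and imbalance up to about 0.5 SD, stepwise and fixed models both cover at about 0.94-0.96. Stepwise coverage falls to about 0.91-0.92 only when a weak confounder differs by 1 SD between phases.

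The type I error of about 6-11% applies if patients are treated as independent and community-by-period survival varies with an SD of 0.5 to 1 point. That SD is an assumption; the documents give no estimate. Stable differences between communities largely cancel, since the same communities contribute to both phases.

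The change is worth making because it is cheap and removes an avoidable weakness from the analysis of the main objective.

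**What to change.** Replace the univariate and stepwise regression with one pre-specified logistic model for each outcome, with no selection step:

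- Force in phase, age, sex, EMS response interval and witnessed status.
- Enter community as a random intercept or as a stratum, not as 18 free indicators.
- Allow for community-by-period variation with a random effect or with cluster-robust standard errors corrected for the small number of clusters.
- State whether initial rhythm stays in the main model. The Background says that without CPR or defibrillation electrical activity passes to asystole, so bystander CPR may affect the recorded rhythm and adjustment could remove part of the effect under study. If it is taken out for that reason, say so and keep it in a sensitivity analysis.

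The cost is a change of wording, plus a check that witnessed status is available for both phases in all communities; the article shows it for the pilot and otherwise speaks only of system and victim characteristics collected since 1994. Intervals will be slightly wider.
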